### Participant recruitment

The trial subjects will be recruited from the outpatient and the ward in the Section II of Endocrinology & Nephropathy department and the community around the Dongzhimen hospital. A multipronged approach is used to identify potential participants to reach the required sample size: ①Advertisement through posters and pamphlets (placed/distributed at various locations including these notice boards in hospitals, outpatient receptions, communities, parks, and health clinics), in which brief description of the subjects that are eligible and details of contact and necessary contributions as participants would be covered. ②An incentive of 100¥ would be offered to physicians or resident doctors for each patient referred by their practice who could be successfully recruited for the trial.③Door-to-door visits in surrounding communities that have the collaboration with Dongzhimen hospital at various times. The investigator will introduce the protocol as well as the benefits and risks to the enrolled participants and an informed consent form is mandatory before the study.

Patients recruited from other hospitals through advertisement will be required to undergo a week of observation, including the control of blood glucose, medication compliance, and degrees of resistance. Following the observation, subjects that meet the inclusion criteria can then be admitted into this clinical trial. The following basic personal information will be collected: sex, age, body mass index (BMI), educational background, occupation, marital status, past medical history, etc. Patients’ personal information is under the supervision of the Data Monitoring Committee (DMC), and this information is protected and will not be disclosed to any individual or organization unrelated to this study.

### Randomization and blinding

#### Sequence generation

This clinical research adopts a randomized, double-blind, parallel-group study method. Patients who meet the criterion of T2DM are randomly divided into the control group and the experimental group. Randomization is achieved by using the random number table method in Statistical Analysis System (SAS 9.2), which is operated by a statistician blinded to treatment and data collection.

#### Allocation concealment mechanism

The random number sequence generated by the system will correspond to the number of the sixty subjects one by one. These numbers are then arranged from small to large (in those with the same random number, the one which is picked out first will be arranged in the front). One to 30 will be designated as the experimental group while 31–60 are the control group. The documents of the random process and randomization list will be enclosed in an opaque envelope. Participants, researchers, and coordinators together with statisticians are not aware of the allocation of the patient and remain unaware until trial completion. The randomization of allocation and concealment of allocation are completed by two researchers who do not communicate with each other.

#### Implementation

The group manager will send an answer form to the investigator who is not involved in assessing the outcome of the study. This form will include a randomization number. The closed envelopes with printed randomization numbers on them are available. For every randomization number, the corresponding code of the randomization list will be found inside the envelopes. The investigator will open the envelope and will find the appropriate drugs to be conducted in this patient without giving the information about treatment allocation to the patient. Staff responsible for recruitment and following up is not allowed to receive information about the group allocation. The allocation sequence will be generated by the Key Laboratory of Chinese Internal Medicine of the Ministry of Education. Throughout the study, the randomization will be conducted by Section II of Endocrinology & Nephropathy department in order to keep the data management and the statistician blind against the study condition as long as the data bank is open. The randomization list remains with the group manager for the whole duration of the study. Thus, randomization will be conducted without any influence of the principal investigators, statistician, or physician.

#### Blinding

In this trial, we use the simulation agent made of dextrin and condiment as the placebo. Both RG formula and placebo are manufactured by Kang Taisheng Pharmaceutical Co., Ltd. with the same specification, appearance, and flavor. The independent statistician, along with the Ethics committee of the study center, is responsible to monitor and assess the blinding procedure as part of data monitoring. The blind code will be disclosed after completion of the statistical analysis.

### Intervention

Patients in both groups are given the same diabetes education and lifestyle intervention. After basic blood glucose control, the fasting blood glucose is stable at less than 7 mmol/L and postprandial blood glucose is stable at less than 10 mmol/L. In this process, metformin, GSDI (α-glucosidase inhibitor), DPP-4 (dipeptidyl peptidase 4) inhibitor, and GLP-1 (glucagon-like peptide-1) analogue are avoided. Insulin and insulin secretion promoters are allowed. On the basis of standard treatment, the experimental group is given a TCM granule packet. Each packet contains 11 g RG formula, which includes 10 g Coptis root and 1 g ginseng. Patients will take RG formula at least for 3 months, once daily, 11 g each time. The control group is given the same amount of Chinese medicine simulation agent which is taken by the same way. The simulation agent contains dextrin and condiment, which looks and tastes exactly like the RG formula. The course of intervention is 12 weeks, and medicine is given every 4 weeks. Serum and stool samples are collected at baseline and at week 12 for relevant indicators. During the trial, the subjects are forbidden to use other TCM drugs (including proprietary Chinese medicine, TCM injections, etc.). For patients that have other chronic and/or complicated diseases that require long-term control/lifetime medication that does not contradict with inclusion criteria, thus, they can be exempted from medicinal limitation; however, this information should be recorded in detail in the case report form (CRF). Follow-up observation is continued after 12 weeks of administration to determine the subsequent effects of the drug. Dongzhimen Hospital affiliated to Beijing University of Chinese Medicine has insurance to cover for non-negligent harm associated with the protocol. This will include cover for additional health care, compensation, or damages whether awarded voluntarily by the sponsor or by claims pursued through the courts. Should this study provide evidence of the effectiveness of RG formula in controlling blood glucose and relieving discomfort, it will be recommended for the patients to continue taking the medicine with a half or less dose as the dietary supplements. The detailed component of this formula will be informed to subjects and these two traditional herbs are common and available in most pharmacies as over the counter. If the subjects are prone to receive the conventional medicine, the consultation services on the online platform will be provided up to 3 months to help patients to develop a personalized glycemic schedule. This study has been approved by the Ethics Committee of Dongzhimen Hospital.

### Outcome measures

The physical condition of patients should be recorded at baseline, week 4, week 8, and week 12.

At the start of the trial, patient’s general information including name, gender, age, education, marriage condition, BMI, etc., will be collected. The complications of diabetes such as diabetic retinopathy, diabetic nephropathy, diabetic peripheral neuropathy, and diabetic peripheral vascular disease should be noted. Other diseases and their corresponding treatment, symptoms, tongue and pulse condition of TCM should also be collected. At week 4 and week 8, two follow-up visits are conducted to collect TCM-related indicators such as symptoms, tongue signs, pulse signs, and symptom diagnosis. At week 0 and week 12, fecal samples and blood samples are collected for quantitative determination of gut microbiota, serum biochemical indicators, and inflammatory indicators.

Stool sample measuring is based on the 16S rRNA sequencing technology of microbiome. It will detect qualified environmental microbial DNA extraction and make the PCR amplification for the general area in V3-V4 primer in DNA base sequence of the designated areas. After a large number of replicated increments, the result will be compared to the existing databank. When the sample passes the inspection, DNA data will be uploaded to Illumina Hiseq 2500 high-throughput sequencing platform for OTU annotation and relative abundance analysis, so as to calculate the species abundance of all samples at phylum, class, order, family, and genus levels. On the basis of these results, the clustering of species abundance, association analysis of common specific OTU, and inter-group differential species analysis will be completed.

Measures of blood samples are divided into biochemical index and inflammation index. As for biochemical index, FBG and PBG are measured by hexokinase method, HbA1c by glycosylated hemoglobin automatic analyzer using the ion-exchange HPLC method, insulin and C peptide by the chemiluminescence method, urea by the colorimetric method, creatinine values by the sarcosine oxidase method, and ALT and AST by the rate method. As for inflammatory indicators, IL-6, TNF-α, and CRP are determined by professional operators using relevant detection kits and enzyme-labeled analyzer (Infinite F50).

#### Primary outcomes

The primary outcome in this study is glycosylated hemoglobin (HbA1c), which means the comparison of HbA1c change between two groups after 12 weeks of intervention. HbA1c is a critical indicator for the diagnosis of T2DM, which can reflect average levels of glycemia during the preceding 3 months and is widely used for diabetic complication assessment [28]. It is considered the gold standard for predicting glycemia-associated risks for the microvascular and macrovascular complications of diabetes mellitus over 5–10 years [29]. Therefore, the value of HbA1c in the care of patients with T1DM and T2DM is unassailable [30]. Professional societies, public health organizations, regulatory agencies, patients, and clinicians have focused on HbA1c levels to gauge the quality of diabetes care, and over time, HbA1c level has supplanted other indicators of the quality of diabetes care, such as blood glucose levels and symptoms of hyperglycemia, despite being a surrogate rather than a direct marker of glycemic control [31]. In addition, careful regulation of blood glucose concentrations in patients with diabetes mellitus normalized HbA1c over 6 weeks [32], so it has also excellent reliability and validity and is sensitive enough for clinical and research practice.

#### Secondary outcomes

The secondary outcomes are mean changes in FBG, PBG, FIL, C-P, IRI, inflammatory factors, and species abundance of gut microbiota. FBG, PBG, FIL, and C-P will be measured to further assess the status of insulin resistance. PBG is obtained by rapid detection of fingertip blood. FBG, FIL, and C-P are obtained by venous blood sample which will be collected after an overnight by a trained medical officer/investigator and transported to a standard laboratory for analysis. Laboratory technicians are blinded to the study participants. The insulin resistance index of the homeostasis model is based on the formula developed by Matthews [33]. The inflammatory factors include interleukin-6 (IL-6), tumor necrosis factor α (TNF-α), and C-reactive protein (CRP). The species abundance of gut microbiota will be based on the second-generation high-throughput sequencing technology.

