## Methods

### Study design

This protocol is designed as a randomized and placebo-controlled trial. Participants and investigators are blinded. A total of 60 subjects will be recruited at the Section II of Endocrinology & Nephropathy department of Dongzhimen Hospital affiliated to Beijing University of Chinese Medicine. They will be randomized in a 1:1 ratio to an experiment group (RG formula) and a control group (placebo). Patients in both groups are given basic blood glucose control. Only the use of insulin and insulin secretion promoters (such as thiazolidinedione and sulfonylurea) can be allowed as basic control in both groups, as current research has shown no significant influence on gut microbiota in neither drugs. The trial flow diagram is illustrated in Fig. 1. The SPIRIT Checklist is shown in Supplemental file 1 [26].

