#### Exclusion criteria

Patients are excluded if any of the exclusion criteria are met: (1) new-onset of T2DM, who should take metformin orally as recommended by guidelines ; (2) patients with cardiac insufficiency (B-type natriuretic peptide is greater than the upper limit of normal) or with impaired liver function (alanine transaminase and aspartate aminotransferase are twice greater than the upper limit of normal) or impaired kidney function (serum creatinine is greater than the upper limit of normal) or mental illness; (3) patients who had diabetic ketosis, diabetic ketoacidosis, or severe infection within 1 month before recruitment; (4) patients who are allergic to Coptis root or ginseng; (5) patients who receive antibiotics and weight-reducing medicine or have participated in other clinical trials within 1 month before recruitment; (6) patients who have inflammatory bowel diseases like ulcerative colitis and Crohn’s disease; and (7) pregnant or lactating women.

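### Fasting insulin and the homeostasis-model index are read as insulin resistance without regard to permitted injected insulin, so in insulin users they may partly reflect dose

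*Protocol article*

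**What the plan says.** **Background therapy.** Under Study design: "Only the use of insulin and insulin secretion promoters (such as thiazolidinedione and sulfonylurea) can be allowed as basic control in both groups". The Intervention section repeats this ("Insulin and insulin secretion promoters are allowed") and says that metformin, α-glucosidase inhibitors, DPP-4 inhibitors and GLP-1 analogues are avoided.

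**Eligibility.** No inclusion or exclusion criterion refers to insulin use. The first exclusion is "new-onset of T2DM, who should take metformin orally as recommended by guidelines", so the trial recruits people with established disease.

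**Outcomes.** Under Secondary outcomes: "The secondary outcomes are mean changes in FBG, PBG, FIL, C-P, IRI, inflammatory factors, and species abundance of gut microbiota". The purpose is given as "FBG, PBG, FIL, and C-P will be measured to further assess the status of insulin resistance". On the index, the text reads "The insulin resistance index of the homeostasis model is based on the formula developed by" the author of a cited reference; the formula is not written out. Neither FIL nor IRI is limited to participants who do not inject insulin, and C-peptide is not tied to the index.

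**Assay.** Outcome measures gives "insulin and C peptide by the chemiluminescence method", with nothing on whether injected and endogenous insulin are told apart.

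**Timing and analysis.** In Table 1, fasting insulin and C-peptide are taken at baseline and week 12, and medication is recorded at screening and at every visit. The Statistical analysis section mentions covariance analysis only in connection with baseline HbA1c.

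**The concern.** A homeostasis-model index reads fasting insulin as the body's own response to fasting glucose. In someone who injects insulin, a serum value that includes the injected product no longer has that meaning. The same holds for fasting insulin when it is taken as a marker of resistance.

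Whether RG improves insulin resistance is one of the questions set out at the end of the Background, and the third aim relates clinical assessments to microbiota and cytokines. An error in FIL or IRI would carry into both.

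The harmful case is specific. The Background cites inhibition of intestinal α-glucosidase as one way in which the formula lowers postprandial glucose. If glucose fell by that route and less insulin were then injected, FIL and IRI would fall and be reported as improved resistance, although resistance had not changed.

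**Working it through.** The plan gives no figure to reproduce. The check sets the sections side by side and then illustrates the mechanism.

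**Step 1. Do the provisions conflict?** Insulin is allowed in both arms (Study design, Intervention). Insulin users are not excluded (Inclusion and Exclusion criteria). FIL and IRI are unrestricted and are given a resistance reading (Secondary outcomes). Together these mean that FIL and IRI will be computed and read as resistance in insulin users.

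**Step 2. One person's index (illustration).** Assumed formula: IRI = FIL (mU/L) × FBG (mmol/L) / 22.5. Assumed endogenous fasting insulin: 10 mU/L. FBG is taken within the article's condition that "the fasting blood glucose is stable at less than 7 mmol/L".

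| Detected injected insulin (mU/L) | IRI at FBG 6.0 | IRI at FBG 6.9 | Ratio |
|---|---|---|---|
| 0 | 6.0 × 10 / 22.5 = 2.67 | 3.07 | 1.0 |
| 5 | 6.0 × 15 / 22.5 = 4.00 | 4.60 | 1.5 |
| 10 | 6.0 × 20 / 22.5 = 5.33 | 6.13 | 2.0 |
| 20 | 6.0 × 30 / 22.5 = 8.00 | 9.20 | 3.0 |

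This is the absolute index at one time. It is not the trial's estimand.

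**Step 3. What survives in the comparison of changes.** Write a user's measured insulin as E + X, with E endogenous and X the detected injected part. The change in FIL is (E12 − E0) + (X12 − X0). If X is the same at both times it cancels from the change in FIL. It also cancels from the change in IRI if glucose is the same at both times; otherwise X × (G12 − G0) / 22.5 remains. Randomisation balances baseline use on average. A stable dose therefore mainly adds variance. Bias needs X12 − X0 to differ between arms.

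**Step 4. Size of that bias under assumptions.** Let p be the share of insulin users (equal in both arms) and d the between-arm difference in mean change of X among users. The artefact in mean FIL change is p × d. At constant FBG 6.5 mmol/L, the artefact in mean IRI change is p × d × 6.5 / 22.5.

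| p | d (mU/L) | FIL artefact (mU/L) | IRI artefact |
|---|---|---|---|
| 0.2 | 2 | 0.4 | 0.12 |
| 0.2 | 10 | 2.0 | 0.58 |
| 0.4 | 5 | 2.0 | 0.58 |
| 0.6 | 2 | 1.2 | 0.35 |
| 0.6 | 10 | 6.0 | 1.73 |

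The documents give neither p nor d, and d also depends on how far the assay detects the product used.

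**The case against.** The strongest reply is that the trial compares mean changes between randomised arms. Glucose must be stable at entry and no insulin titration during the 12 weeks is described, so a constant injected contribution largely drops out. This stands, and it limits the harm in that case mainly to lost precision. It does not remove the problem. The article does not say that background insulin stays constant, and under Adherence to study medication participants upload home glucose readings and glycaemic results are available at once, so differing dose changes are possible.

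A second reply is that C-peptide is already a separate secondary outcome, medication is recorded, and subsets or covariates for a secondary outcome can be left to an analysis plan. This stands in part: resistance is not judged on FIL and IRI alone, and analytic detail may exist elsewhere. But the article itself fixes the permitted drugs, the population, the outcomes and their interpretation, and these do not fit together for insulin users.

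A reader might infer three stronger claims that the documents do not support:

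- *That the result is wrong by 50% to 200%.* Those ratios describe one person's absolute index under assumed values, not a between-arm difference in change.
- *That many participants inject insulin and that all of it is counted.* Avoiding four drug classes and excluding new-onset disease make insulin use likely, but no share is stated, oral drugs are also allowed, and assay specificity is unknown.
- *That calling thiazolidinedione a secretion promoter adds to the error.* It is an insulin sensitiser, so the label looks wrong. A drug that truly alters resistance is not measurement error, and stable use is balanced on average by randomisation.

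**Conclusion.** The concern holds as a limit on how FIL and IRI can be interpreted in insulin users. Followed as written, the plan reads these two outcomes as resistance in people whose measured insulin may include injected drug. With stable doses the main consequence is noise, which matters with 30 per arm. With doses that change differently between arms, the comparison is biased, and reduced insulin need under RG would appear as improved resistance.

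The size is not derivable from the documents. The range of 0.12 to 1.73 in mean IRI change (0.4 to 6.0 mU/L in mean FIL change) rests wholly on the assumed formula, user shares, between-arm differences and constant glucose. The point concerns two secondary outcomes; the HbA1c comparison is not affected by this measurement problem. It is worth correcting, but it does not threaten the trial's main conclusion.

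**What to change.** In Secondary outcomes, and before the blind is broken:

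1. Make the main analysis of FIL and IRI the participants not using insulin at baseline, as recorded before randomisation. Adjust for the baseline value of the outcome and baseline background drug class. Do not define the subset by week-12 insulin use: treatment may affect it, and selecting on it would break the randomised comparison.
2. Report an index from fasting C-peptide and fasting glucose in all participants, stratified by baseline insulin use, as supportive only. Injected insulin can suppress C-peptide, so reduced insulin need could raise C-peptide and push this index the other way. It cannot simply replace IRI.
3. Handle insulin started or changed during the 12 weeks in a sensitivity analysis, using the medication records in Table 1.
4. Separately, correct the description of thiazolidinedione under Study design, so that drug class is coded correctly for the adjustment. This is a wording and coding change only.

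**Cost.** No new samples or visits. Precision for FIL and IRI falls. With an assumed 20% to 60% of users, the main analysis keeps 30 × 0.8 = 24 down to 30 × 0.4 = 12 per arm before drop-out. At an unchanged SD, the standard error grows by 1/√0.8 = 1.12 to 1/√0.4 = 1.58 times; removing insulin users may also lower the SD and offset some of this. The result then applies to non-users of insulin, which should be stated.

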#### Safety assessment

Safety indicators including blood routine and urine routine and liver and kidney function are measured before and after the study. Adverse events, such as hypoglycemic reactions, constipation, and abdominal pain, are recorded in detail and their association with medication is determined by professional researchers. The trial can be terminated if necessary. During the study period, the adverse event record form is completed to record the duration, occurrence time, severity, measures, and outcome of the adverse event. The severity of the adverse events is divided into mild, moderate, and severe. Mild can be perceived as a tolerable adverse effect and does not require immediate medical attention; moderate is intolerable and requires special treatment; severe discomfort requires timely termination of the trial and immediate emergency treatment. Researchers will report it to the person in charge of the trial, the sponsoring unit, and the medical ethics committee in time, and even report it to the adverse reaction center according to the relevant regulations of the State Medical Products Administration. The ethics committee have the right to make the final decision if termination is needed.

In this study, Coptis root is known to have the effect of promoting blood circulation and dissipating blood stasis. Therefore, the risk of increased menstrual bleeding should be clearly informed when female subjects are enrolled. Aside from signing the informed consent, the female subjects are also instructed to take a bag of drugs 2–3 times during menstruation to reduce the peak blood drug concentration and the risk of heavy menstruation. Last but not least, if the amount of bleeding is large, an authorized clinician should complete the judgment of causality and exclude the menstrual abnormalities caused by other factors, such as the combined effect of conventional drugs, the progress of the subject’s primary disease, and other treatment measures. Should large menstruation is confirmed and recorded as adverse reactions, the reduction of dosage or drug withdrawal would be necessary. In addition, there is also the possibility for patients to experience diarrhea, abdominal pain, and secondary constipation. If diarrhea and abdominal pain occur, then the patients will be suggested to take the medicine within 30 min after the meal so as to reduce the direct stimulation of Coptis root in the gastrointestinal tract. If constipation appears, then patients are suggested to take the medicine with honey, as TCM herbal theory believes it has the effect of promoting bowel movement by moistening the large intestine.

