### Adherence to study medication

Strategies to improve adherence to intervention protocols include:

(1) Providing professional lifestyle guidance, 2 weeks of TCM treatment, and laboratory index containing liver function, kidney function, HbA1c, fasting blood glucose, postprandial blood glucose, and gut microbiota for free. The outcomes of HbA1c, fasting blood glucose, and postprandial blood glucose are instantly available

(2) Subsidizing the cost of patients’ travel to the hospital for visits

(3) Adding the patient’s network contact address, communicating and solving the patients’ problems at any time, requiring the patient to monitor blood glucose at home regularly and upload blood glucose data, continuing to conduct diabetes education

(4) Checking the number of medicine bags left by the patients at each return visit, as well as confirming the situation of medication

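### The menstruation instruction does not fit the once-daily schedule, treatment duration is worded two ways, and honey is suggested without limits: the passages need reconciling, though few participants and days are affected

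*Protocol article*

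**What the plan says.** **Schedule.** The Intervention section states "Each packet contains 11 g RG formula, which includes 10 g Coptis root and 1 g ginseng" and "Patients will take RG formula at least for 3 months, once daily, 11 g each time".

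**Menstruation.** The Safety assessment section warns of increased menstrual bleeding and adds that "the female subjects are also instructed to take a bag of drugs 2–3 times during menstruation". The purpose given is a lower peak drug level in the blood and less risk of heavy bleeding. The instruction is given in advance, not only once heavy bleeding has occurred.

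**Duration.** Besides the three-month minimum just quoted, the Intervention section says "The course of intervention is 12 weeks, and medicine is given every 4 weeks". It then places follow-up after 12 weeks of administration, to look at later effects of the drug. The abstract, Table 1 and the primary outcome also use 12 weeks. The Adherence to study medication section lists "2 weeks of TCM treatment" among the things provided free of charge.

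**Honey.** The Safety assessment section names constipation as a possible effect and says: "If constipation appears, then patients are suggested to take the medicine with honey".

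**Adherence.** Leftover bags are counted at each return visit, and medication use is confirmed with the patient.

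**The concern.** A participant or dispensing nurse should be able to read off how many bags to take on any given day and when to stop. Three things are at stake.

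- **Safety.** A precaution against heavy bleeding is worded so that one literal reading increases intake on the very days it is meant to protect.
- **Exposure and adherence.** A leftover-bag count means something only against an expected count. For menstruating women that count depends on how the sentence is read. The follow-up measurements of HbA1c, fasting and postprandial glucose and stool in Table 1 describe the period after drug only if drug stops at a fixed time.
- **Co-intervention.** Honey contains sugar. The outcomes include HbA1c, glucose and gut microbiota, and elsewhere the protocol takes care to keep out glucose-lowering drugs and probiotics that could disturb the microbiota. If constipation is caused by the study drug, honey use could differ between arms even though both are blinded.

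**Working it through.** **Inputs from the article:** 10 g + 1 g = 11 g per packet, which reproduces the stated packet size; one packet daily; a 12-week course. Packet and bag are taken to mean the same unit.

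**Assumptions, not in the article:** 3 to 7 days of menstruation per cycle and 3 cycles in 12 weeks.

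**Baseline count.** 12 × 7 = 84 days, so 84 bags and 84 × 11 = 924 g.

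**Menstruation sentence.** With L days per cycle there are 3L menstruation days.

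| Reading | Intake on those days | Bags over 12 weeks | L = 3 | L = 5 | L = 7 |
|---|---|---|---|---|---|
| One daily bag in 2–3 portions | 11 g per day | 84 | 84 | 84 | 84 |
| A whole bag 2–3 times a day | 22–33 g per day | 84 + 3L to 84 + 6L | 93–102 | 99–114 | 105–126 |
| A whole bag 2–3 times per period | 22–33 g per period | 84 − 3L + 6 to 84 − 3L + 9 | 81–84 | 75–78 | 69–72 |

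Each reading against the Intervention section:

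- Portions: the daily total agrees, but dosing is no longer once daily or 11 g each time.
- Whole bags several times a day: frequency and daily total both disagree.
- Whole bags a few times per period: dosing is no longer daily.

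Each reading against the stated purpose:

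- Smaller portions lower the peak.
- Whole bags several times a day do not.
- A whole bag on fewer days leaves the peak after each dose as it was.

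The purpose therefore points to portions, but the reader has to infer this.

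**Duration.** Three calendar months are about 91 days (89 to 92). Against 84 days that is 91 / 84 = 1.083, or about 8% more, and a stated minimum has no upper end. The two-week figure would be 14 bags. That matches neither duration nor the four-weekly dispensing, but its place in a list of free items suggests it is not a course length.

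**Honey.** No arithmetic applies. The article gives no amount and no constipation rate, so no effect on HbA1c can be derived from it. The Safety assessment section has the adverse event form record the measures taken, so the fact of honey use may be captured. Nothing asks for its amount or dates.

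**The case against.** The strongest reply is that the purpose clause settles the menstruation sentence. Only one bag taken in portions lowers the peak, so the sentence is an exception to once-daily dosing, with the daily total and bag count unchanged. Likewise, three months is a loose restatement of 12 weeks. Table 1 separates medication weeks from follow-up weeks, and the Intervention section puts follow-up after administration. Honey advice applies in both blinded arms. If honey were used more on active drug, its sugar would work against a glycaemic benefit rather than create one. Adherence does not rest on bag counts alone, no analysis set in the article is defined by them, and the adherence-based withdrawal rule covers only the run-in. Operating detail may also sit in the procedures manual or the consent form.

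Much of this stands. A reader might infer that the packets-per-day instructions flatly contradict each other, or that exposure, adherence and safety cannot be interpreted. The article supports neither. The likeliest reading keeps 11 g per day, the sentence touches only menstruating women on some days, honey touches only participants with constipation, and the primary time point is 12 weeks everywhere. The widest spread of bag counts lies between the two readings that the purpose clause makes less plausible, so it is not a measure of the likely error.

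What does not fall away is that the published sentence fits the once-daily schedule on no reading, and that a bleeding precaution should not have to be inferred from its rationale. Also, the direction of a honey effect on the microbiota outcomes cannot be argued from the article.

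**Conclusion.** The point holds as an inconsistency of limited reach.

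- **Menstruation instruction.** It conflicts with the Intervention section at least on frequency and amount per dose. On the likeliest reading the effect on daily total and bag count is zero. On the whole-bag reading intake is two to three times the stated daily amount on the affected days. The counts in the table rest on the assumed 3 to 7 days and 3 cycles. The number of menstruating participants is unknown in a trial that enrols adults aged 18–65.
- **Duration.** The two statements differ by about 7 days, plus an open end that does not sit with a post-drug follow-up. The primary comparison at 12 weeks is not put in doubt.
- **Honey.** It is a real sugar-containing co-intervention, only partly captured by adverse event recording. It could be unequal by arm if constipation is drug-related. Its size cannot be estimated from the article.

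**What to change.** - Reconcile the Intervention and Safety assessment sections into one explicit statement of bags per day, including on menstruation days, and one duration consistent with an off-drug follow-up. Carry the same wording into the patient instructions, so that the leftover-bag count has a single expected value.
- In Adherence to study medication, make clear that the two-week figure is not a course length, if that is so.
- Add two case report form fields: days on the modified menstruation schedule, and honey use with amount and dates. Report both by arm.
- Have the clinical lead and the ethics committee reconcile the honey advice with the glycaemic endpoints.

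Which dose, schedule or remedy is right is for them to decide; none is proposed here.

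The cost is wording, an ethics notification and two form fields. If the reconciled text counts as a change that may affect safety, the Ethics and dissemination section requires a formal amendment. With 44 of 60 participants recruited according to Trial status, 60 − 44 = 16 were still to be enrolled, so the clarification could still reach them and anyone then on treatment.
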